However, this body of evidence consists primarily of studies conducted in the United States (US) [1, 3, 4], Europe [1, 2], or Australia [1], and there are limited data on the effects of CGM on clinical outcomes in low- and middle-income countries (LMICs), where CGM devices may not be readily available. A recent scoping review of CGM in LMICs did not identify any randomised trial conducted in Sub-Saharan Africa [5], and to our knowledge only one study on the use of CGM in people with T1D has been conducted in the region, which was a feasibility study in Kenya and Uganda and not a randomised control trial [6]. Similarly, we have identified no randomised trials conducted in South Africa that have evaluated the impact of CGM compared with standard of care glucose monitoring on HbA1c (and other clinical outcomes) in people with T1D, with the majority of the evidence base consisting of qualitative, mixed methods, and perception studies [7–10]. Overall, there exists a substantial evidence gap on the use of CGM in people with T1D in LMICs, particularly those in Sub-Saharan and Southern Africa, and while some devices have received US Food and Drug Administration (FDA) approvals or European Commission “Conformité Européenne” CE marks [11], further empiric evidence is needed to inform policy decision around their use in these countries as evidence generated in higher resource settings may not be applicable [11–13].

The rationale for selecting Kenya and South Africa as study locations is rooted in different reasons. In South Africa, 31,500 people live with T1D, with an annual growth rate of 6.1% [14]. In Kenya, there are 23,100 people living with T1D, with an annual growth rate of 4.2% [15]. There are different levels of care provision for T1D in both countries, which translates into different approaches to T1D management. Additionally, there are different levels of CGM availability in both countries.

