## Interventions

### Explanation for choice of comparators {6b}

The comparator is standard of care diabetes management at each trial clinic (glucose monitoring) by participants assigned to Arm 3, their HbA1c levels and all the data collected from their case report forms (CRFs).

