### Outcomes {12}

#### Primary outcome

The primary endpoint will be the mean change from baseline (pre-CGM device use) HbA1c at various timepoints up to 15 months (percentage and mmol/mol). This will be assessed in all trial arms and presented as absolute values and percentage changes, together with summary statistics and statistical comparisons (between group).

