### Sample size {14}

Assuming a change in HbA1c levels of 2% after continuous use of a CGM device (determined by expert consultation) and an effect size of 0.2, a sample size of 246 participants (82 in each arm) would be required to achieve 80% power to detect within- and between-group differences at the 5% significance level (using repeated measures analysis of variance [ANOVA]).

For qualitative assessments, sample sizes will be pragmatically derived and will vary based on the number of available respondents and attainment of information/thematic saturation. In Kenya, the target populations will be 30 for focus group discussions and HRQoL surveys (10 in each arm) and 10 for semi-structured healthcare provider interviews. In South Africa, the target populations will be 45 for focus group discussions and HRQoL surveys (15 in each arm) and 10 for semi-structured healthcare provider interviews.

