#### Primary outcome

Between-group analyses of the primary outcome will be conducted using the Fully Complied or Partly Complied populations and two-way repeated-measures ANOVA with time and arm as independent variables.

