### Methods for additional analyses (e.g. subgroup analyses) {20b}

No prespecified subgroup analyses are planned. However, sensitivity analyses will be performed to assess the uncertainty surrounding cost estimates and to identify the key assumptions that drive those costs, by adjusting various input parameters.

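### The stated primary model names only time and arm, so it gives up precision that adjusting for baseline HbA1c and clinic would recover

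*Protocol article*

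**What the plan says.** The endpoint, under Outcomes {12}, is the "mean change from baseline (pre-CGM device use) HbA1c at various timepoints up to 15 months". The primary paragraph of Statistical methods {20a} analyses it by "two-way repeated-measures ANOVA with time and arm as independent variables". The secondary paragraph gives the same two factors for the quality-of-life outcomes. For between-group GMSS scores it gives them again, in a two-way or one-way version depending on the data available. Nowhere does the article add a baseline covariate or a clinic or country factor, and Sequence generation {16a} mentions no stratification. Section {20a} does call itself a brief outline and refers to a separate SAP for detail.

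On setting, the Background says: "There are different levels of care provision for T1D in both countries, which translates into different approaches to T1D management". The same section adds that the design varies slightly by centre because routine care does. Section {6b} says: "The comparator is standard of care diabetes management at each trial clinic". Section {20b} says: "No prespecified subgroup analyses are planned".

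Sample size {14} takes "an effect size of 0.2" and 246 participants (82 per arm) for "80% power to detect within- and between-group differences at the 5% significance level".

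**The concern.** Baseline HbA1c is measured anyway and can be expected to predict follow-up HbA1c. Subtracting it, or treating it as a time level, amounts to fixing its regression slope at 1. Estimating the slope is at least as precise in large samples, and clearly more precise when the correlation between baseline and follow-up is moderate. Leaving clinic out means that chance imbalance between arms across six dissimilar clinics is not adjusted for. At stake is the width of the confidence intervals for the primary result and for the quality-of-life and satisfaction scores, from the same participants. A smaller matter is interpretation: if both countries are combined, one arm difference is averaged over settings in which, by the article's own account, care and comparator differ.

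**Working it through.** **1. The plan's own figure.** Inputs from Sample size {14}: effect size 0.2, three arms, 5% level, 80% power. Read as Cohen's f in a one-way ANOVA, the noncentrality is f² × N = 0.04 × 246 = 9.84 on 2 and 243 degrees of freedom. Power is 0.804, and 82 per arm is the smallest number that reaches 80%. The stated 246 is reproduced. The repeated-measures formulas tried did not give it: 111 to 222 for the between-arm test (2, 4 or 5 measurements, correlation 0.3 to 0.8) and 27 to 126 for the arm-by-time interaction (correlation 0 to 0.7). So 246 takes no credit for repeated measures or for baseline adjustment.

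**2. Variance with and without adjustment.** Let rho be the correlation of baseline with one follow-up value, with both SDs equal to 1.
- Change score: variance 2(1 − rho).
- Baseline-adjusted: variance 1 − rho².
- Ratio: (1 − rho²) / [2(1 − rho)] = (1 + rho)/2.

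**3. Effect on power.** The article gives no rho; 0.3 to 0.7 is assumed. If f = 0.2 refers to the change score, the noncentrality becomes 9.84 divided by the ratio.

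| rho (assumed) | Variance ratio | Noncentrality | Power at 246 | N for the same power as 246 unadjusted |
|---|---|---|---|---|
| no adjustment | 1.00 | 9.84 | 0.80 | 246 |
| 0.3 | 0.65 | 15.14 | 0.94 | 160 |
| 0.5 | 0.75 | 13.12 | 0.91 | 185 |
| 0.7 | 0.85 | 11.58 | 0.87 | 210 |

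If f = 0.2 instead refers to the follow-up value, the adjusted variance factor is 1 − rho² = 0.91 to 0.51, and adjusted power is 0.84 to 0.98.

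**4. The entry threshold.** Step 2 needs equal SDs. The inclusion criteria require a current HbA1c of at least 10%. If that qualifying value is also the trial baseline, its SD shrinks. Example: rho 0.5 before selection, baseline cut at its mean.
- Baseline variance falls from 1 to 1 − 2/π = 0.363.
- The adjusted variance stays at 0.75.
- The change-score variance is 0.25 × 0.363 + 0.75 = 0.841.
- The ratio is 0.75/0.841 = 0.89, a gain equivalent to 12% more participants, against 33% (1/0.75) without selection. Power at 246 is about 0.85.

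**5. Clinic.** Stable differences in HbA1c level between clinics largely cancel in a change; only differences in change remain. If clinic or country explains an assumed 2% to 10% of residual variance, power moves from 0.80 to 0.81–0.85. Most of the gain therefore comes from baseline.

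**6. Which value is the baseline.** Table 1 (Kenya) schedules HbA1c on Day 1. Table 2 (South Africa) schedules the first HbA1c at Week 1 (Visit 2), after device application on Day 1. Outcomes {12} defines baseline as before device use, and the Partly Complied population requires a value at Visit 1. These passages must be reconciled before any baseline covariate is defined. Step 4 also depends on the answer.

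**7. Country estimates.** Sample size {14} does not say whether 246 is per country or for both. If it covers both, split equally (an assumption), each country has 41 per arm. Power for f = 0.2 is then 0.49. The 95% half-width for a pairwise contrast is 1.96 × √(2/41) = 0.43 SD, against 1.96 × √(2/82) = 0.31 SD for all participants together.

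**The case against.** The strongest reply is that covariates are normally fixed in the SAP, which is not shown, and that the article announces only an outline. That stands as far as the SAP is concerned: nothing here shows that it omits adjustment. It does not clear the article, which names both the method and its independent variables. An SAP that follows the article inherits that model.

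Four stronger readings are tempting, and the documents do not support them.
- *Baseline is ignored.* It is not: it is the reference for change or a level of time. Only covariate adjustment is missing.
- *The countries are pooled and no country result is planned.* One trial, one sample size and one model suggest pooling. But there are two registrations, the schedule tables are titled as separate Kenyan and South African studies, and section {20c} speaks of SAPs in the plural. Ruling out subgroup analyses does not rule out a separate analysis in each country.
- *The entry threshold makes change scores worse still.* It lowers the correlation, but when the truncated value is itself the baseline it also shrinks the baseline SD, and the gain from adjustment falls (step 4). The inference could hold if eligibility rests on a separate earlier value, as the 3- and 18-month windows allow.
- *The unadjusted analysis starts at 62% or 76% power.* Those figures (rho 0.3 and 0.5) need a pairwise effect of 0.42 SD of a single HbA1c value. This can be derived from f = 0.2 if one arm differs from the other two (0.2 × 3/√2 = 0.42), but Sample size {14} does not state it. The stated f of 0.2 with 82 per arm gives about 80%.

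**Conclusion.** The point holds as a loss of efficiency in the model as written, not as a threat to validity: randomisation protects the arm contrast with or without the covariates. For one follow-up visit with equal SDs, adjustment would reduce the variance to 0.65–0.85 of the change-score variance, worth 54% to 18% more participants (1/0.65 and 1/0.85). On the change-score reading of the effect size, power would go from about 0.80 to 0.87–0.94. These sizes rest on an assumed rho of 0.3 to 0.7 and shrink towards the step 4 result if selection narrows the baseline. Clinic contributes little precision. Whether the countries are pooled is an open question that the sponsor should answer, not an established defect. The change is worth making because it costs almost nothing and can be prespecified: section {20c} has the SAPs finalised before any analysis.

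**What to change.** 1. Reconcile Table 2 with the endpoint definition and the Visit 1 requirement, and state which HbA1c value is the baseline in each country. The covariate cannot be defined until this is done.
2. Restate the primary model: post-baseline HbA1c as the outcome, with arm, visit, arm-by-visit, baseline HbA1c (with its visit interaction) and clinic. Clinic also absorbs country.
3. Use the same structure for the quality-of-life and GMSS analyses, each with its own baseline score.
4. State whether the two country studies are analysed together. If they are, report the arm differences for Kenya and South Africa as estimates with confidence intervals, not as separate tests.

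The cost is wording and a few degrees of freedom: five for six clinics, plus those for baseline and its interaction. Apart from settling the South African baseline, no new data are needed.

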#### Secondary outcomes

Glucose variation will be assessed using the Intervention population, with %CV calculated as the ratio of the standard deviation to the mean. HRQoL outcomes will be analysed using the Fully Complied or Partly Complied populations and two-way repeated-measures ANOVA with time and arm as independent variables. Within-group mean GMSS scores will be analysed using t-tests and between-group scores using repeated-measures two-way or one-way ANOVA (depending on the availability of data) with time and arm as independent variables (all using the Fully Complied or Partly Complied populations).

All other secondary outcomes will be analysed using descriptive statistics: hospitalisations using the Partly Complied population, adherence using the Intervention population, and cost surveys using the Fully Complied or Partly Complied population.

For the cost analysis, standard bottom-up costing methods from a partial societal perspective will be used to estimate the costs of both direct and indirect resources utilised by participants over the trial period. Unit costs will be assigned to these resource outputs using values sourced from public sources: laboratory test costs from the relevant national laboratory service, staffing costs from the Salaries and Renumeration Commission, medicine and supply costs from Kenya Medical Supplies Authority (KEMSA)/Mission for Essential Drugs (MEDs), minimum wage data from the relevant government agency, and the cost of procedures and in-patient hospital stays from the National Health Insurance Fund. Where necessary, unit costs will be sourced from other publicly available resources and the literature. ICERs will be calculated using the primary outcome measure and the time ‘in-range’, and QALYs will be calculated from the HRQoL outcomes.

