**Methods:**

This trial was designed as a pragmatic, parallel-group, open-label, multicentre, three-arm, randomised (1:1:1) controlled trial of continuous or periodic CGM device use versus standard of care in people with T1D in South Africa and Kenya. The primary objective of this trial will be to assess the impact of continuous or periodic CGM device use on glycaemic control as measured by change from baseline glycosylated haemoglobin (HbA1c). Additional assessments will include clinical outcomes (glucose variation, time in/below/above range), safety (adverse events, hospitalisations), quality of life (EQ-5D, T1D distress score, Glucose Monitoring Satisfaction Survey for T1D), and health economic measures (incremental cost-effectiveness ratios, quality adjusted life years).

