**Discussion:**

This trial aims to address the substantial evidence gap on the impact of CGM device use on clinical outcomes in LMICs, specifically South Africa and Kenya. The trial results will provide evidence to inform policy and treatment decisions in these countries.

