## Methods: Participants, interventions, and outcomes

### Study setting {9}

The trial in Kenya will be conducted at three public sector clinics that are part of the ‘Changing Diabetes in Children’ program: the Kenya Diabetes Management and Information Centre, and the Machakos and Kiambu level five referral hospitals. This program was launched in 2012 to improve T1D care in children and young adults (under the age of 18), by working with the Kenyan Ministry of Health to build capacity and strengthen the local health system through the provision of medical equipment, point-of-care glucose meters, healthcare training, and dissemination of best practice methods [17].

The trial in South Africa will be conducted at three public sector clinics: the diabetes clinic at Groote Schuur Hospital in Cape Town; the paediatric diabetes clinic at Red Cross War Memorial Children’s Hospital in Cape Town; and the adult and paediatric diabetes clinic at Steve Biko Academic Hospital in Pretoria.

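### The single unit-cost rule for the two-country trial takes medicine and supply prices from a Kenyan source, with no South African counterpart

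*Protocol article*

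**What the plan says.** The trial compares "continuous or periodic CGM device use versus standard of care in people with T1D in South Africa and Kenya". Study setting {9} lists three Kenyan clinics and adds: "The trial in South Africa will be conducted at three public sector clinics". So three of the six clinics are South African.

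The cost analysis is described in Statistical methods {20a}, under Secondary outcomes. It covers direct and indirect resources used by participants over the trial and is not limited to either country. Two of its unit-cost sources are worded to fit either country. One is for tests: "laboratory test costs from the relevant national laboratory service". The other is for lost earnings: "minimum wage data from the relevant government agency". Drugs and consumables are treated differently, since the rule there specifies "medicine and supply costs from Kenya Medical Supplies Authority (KEMSA)/Mission for Essential Drugs (MEDs"). Staff time also rests on one named body: "staffing costs from the Salaries and Renumeration Commission". Procedures and in-patient stays are priced from the National Health Insurance Fund. A closing sentence allows other public sources and the literature where needed. ICERs are then built on the HbA1c outcome and on time in range. Outcomes {12} names ICERs and QALYs as the basis for comparing arms. Neither section says whether ICERs are computed by country or pooled.

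**The concern.** Two of the sources are worded to adapt to the country, but the medicine and supply source is not. An analyst who follows the text would apply a Kenyan tariff to South African participants for that category. The resulting total would mix two countries' prices and would not be the cost to either health system.

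This matters because cost to users and providers is a stated secondary objective, and because the abstract says: "The trial results will provide evidence to inform policy and treatment decisions in these countries". The background gives a reason not to assume that one country's tariff fits the other: "There are different levels of care provision for T1D in both countries, which translates into different approaches to T1D management".

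**Working it through.** There is no figure to reproduce: the article gives no unit cost, currency, price year or ICER. The check is a reading of each cost category against its stated source.

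| Category | Stated source | Scope on the face of the text |
|---|---|---|
| Laboratory tests | "laboratory test costs from the relevant national laboratory service" | Follows the country |
| Lost earnings | "minimum wage data from the relevant government agency" | Follows the country |
| Medicines and supplies | "medicine and supply costs from Kenya Medical Supplies Authority (KEMSA)/Mission for Essential Drugs (MEDs") | KEMSA is Kenyan by name; MEDs is paired with it; no South African source |
| Staffing | "staffing costs from the Salaries and Renumeration Commission" | One body, country not stated, no counterpart |
| Procedures and in-patient stays | National Health Insurance Fund | One body, country not stated, no counterpart |

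**Count.** 2 categories follow the country, 1 is Kenyan, and 2 rest on a single body of unstated country: 2 + 1 + 2 = 5. One category of five is therefore Kenyan on the face of the text. It would be three of five only if both bodies of unstated country were assumed to be Kenyan.

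**Applied to a South African participant.** Laboratory tests and lost earnings take South African prices. Medicines and supplies take the Kenyan tariff. Staff time and any admission take whatever the single named bodies publish. The sum is a mixed-country total.

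**What would be needed to size the effect.** Write the incremental cost between two arms as the sum over categories of price × difference in quantity used. For South African participants, the error in the medicine and supply term is

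(Kenyan price − South African price) × (between-arm difference in quantity).

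The article gives none of the three inputs. If the arms use the same quantity, the error cancels from the increment. It remains in each arm's total cost, as (Kenyan price − South African price) × quantity used. The article also does not say whether sensors, the obvious item that differs between arms, are priced as supplies from this source. No numerical size can be attached to any ICER.

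**Is the rule meant for Kenya only?** Elsewhere the article marks country-specific rules openly: the eligibility windows, the qualitative sample sizes and the HbA1c device-accuracy analysis are each labelled by country. The costing paragraph carries no such label, and its use of country-neutral wording for two sources suggests that it was meant for both countries.

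**The case against.** The strongest reply is that this is a condensed article. It defers detail to a separate statistical analysis plan, and Trial status lists separate current protocols for Kenya, Pretoria and Cape Town. A full table of unit-cost sources by country could properly sit there. On this view the paragraph is best read as country-appropriate pricing with incomplete examples, and the fallback sentence covers South African prices, since a Kenyan supply authority is an obvious case where another source is needed.

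Part of this stands. The absence of a complete source list is not a fault in an article, and the fallback does allow South African prices. A reader might infer that it applies only when a named source lacks a price, but the text sets no such limit. Still, the article does more than leave the medicine and supply source open: it names one, and that source fits only one of the two countries. The fallback is permissive and does not make the participant's country a reason to use it. The planned cost sensitivity analyses vary inputs around a base case; they do not set that base case by country.

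The reply is also right about three further inferences:

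- That the whole rule uses Kenyan prices. Two of the five categories follow the country.
- That the staffing and in-patient bodies are Kenyan. The article does not state their country.
- That South African or pooled ICERs are wrong by some calculable factor. Any such factor would rest on invented price ratios and country shares, with no known link to the increment.

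**Conclusion.** The point holds in a limited form. The costing rule covers both countries but ties medicines and supplies to a Kenyan source, and it names a single body for each of staffing and procedure/in-patient costs. Read literally, it values South African medicines and supplies at Kenyan prices. This is a stated choice that does not fit half the clinics, and it is inconsistent with the country-neutral wording used for laboratory and wage costs.

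The conclusion assumes that the paragraph applies to both countries, as its lack of a country label implies, and that the paired medicine and supply source is Kenyan, as KEMSA's name shows. It concerns a secondary outcome, and prices can be reassigned after data collection, so no trial data are at risk. If the country protocols or the analysis plan already name South African sources, the remedy reduces to correcting the published sentence.

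A reader might go further and conclude that ICERs must be reported separately by country. The article does not support that as a correction of an error, because it does not say which kind of ICER is planned. What is needed is that it says so.

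**What to change.** Amend the costing paragraph in Statistical methods {20a} as follows:

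- Take unit costs in every category from public sources for the participant's own country. Keep KEMSA/MEDs for participants at the Kenyan clinics, and use corresponding South African public-sector sources for those at the South African clinics.
- State which country the staffing and the procedure/in-patient sources serve, and name the counterpart for the other country.
- State whether ICERs are calculated by country or pooled. If pooled, express costs in a common currency and price year.

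The cost is a change of wording and a second unit-cost table. No new data are collected.
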